## Abstract

**Background:**

Despite the decline in cigarette smoking prevalence during nearly the past two decades, tobacco use is still widespread in the German adult population, accounting for 125,000 deaths each year and causing tremendous social costs. To accelerate the reduction in tobacco smoking prevalence, evidence-based smoking cessation methods are pivotal to a national tobacco control strategy. The present study aims to evaluate the effectiveness of the national German Smokers Quitline offering cessation support to smokers.

**Methods:**

A total sample of 910 daily smokers, who are motivated to quit, will be recruited via an online access panel and randomly assigned to either the intervention (telephone counselling) or control condition. In the intervention group, participants will receive up to six proactive phone calls during an intervention period of approximately six weeks. The provided treatment will combine the principles of motivational interviewing and those of the cognitive behavioural approach to treating substance use. Participants in the control condition will receive a self-help brochure to support smoking cessation. Data collection will take place at baseline as well as three (post assessment) and twelve months (follow-up assessment) after baseline assessment. Primary outcome measures will include the seven-day point prevalence abstinence at 3-month and 12-month assessments as well as prolonged abstinence (abstinence over the 12 month period). Secondary outcome measures will include a change in smoking-related cognitions and coping strategies among all participants. Among non-abstainers, treatment success indicators such as a reduction in number of cigarettes smoked per day and changes in the number and duration of quit attempts after intervention start will be assessed. It is expected that after both three and twelve months, smoking cessation rates will be higher in the telephone counselling condition compared to the control condition.

**Discussion:**

The results will provide insights into the effectiveness of proactive telephone counselling by the national German Smokers Quitline.

**Trial registration:**

The protocol for this study is registered with the German Clinical Trials Register: DRKS00025343, Date of registration: 2021/06/07, https://www.drks.de/drks_web/setLocale_EN.do

## Background

Despite the decline in cigarette smoking prevalence over the past two decades, cigarette smoking remains the leading cause of preventable disease, disability, and death globally accounting for 8.71 million deaths in 2019 [1]. With 14.4 million current smokers in 2018, tobacco use is still widespread in the German adult population [2]. To further accelerate the reduction in tobacco smoking prevalence, federally available and effective smoking cessation interventions are needed and central to a successful tobacco control policy [3]. International efforts for tobacco interventions have been strengthened by the World Health Organization’s Framework Convention on Tobacco Control (WHO FCTC) [4]. The WHO FCTC has been developed to protect current and future generations from the health, social, and environmental consequences of tobacco use and second-hand smoke [4]. One effective measure proposed by the FCTC is the availability of telephone counselling services to support smoking cessation by trained specialists [5].

Telephone counselling services for smoking cessation are recommended because they have the potential to reach a large number of smokers [6, 7], particularly due to their flexibility in terms of time and location. They can also provide treatment to underserved groups, such as ethnic and/or linguistic minorities [8, 9], to smokers who are geographically dispersed and are attractive to smokers seeking low threshold support [10–13]. Moreover, they have the ability to tailor the intervention to key recipient characteristics and therefore offer individualized tobacco cessation to smokers [14]. Although abstinence rates achieved through telephone counselling are lower than those attained by face-to-face counselling, quitlines are effective [15] and highly cost-effective [16] due to their extraordinary reach of the smoking population [17]. For these reasons, quitlines can be considered a measure with major public health potential [18]. The effectiveness of telephone counselling for smoking cessation has been demonstrated in a systematic review [15], which shows that smokers who had called quitlines and received proactive telephone counselling were 1.38 times more likely to become abstinent than smokers who were supported by self-help materials or brief counselling at a single call (minimal intervention controls). This means that they increased their chances of long-term cessation (at least 6 months after start of the intervention) from 7 to 10%. Moreover, three to five proactive calls seem to be more effective than fewer calls [15].

Germany implemented its national Smokers Quitline in 1999. It is overseen by the Federal Centre for Health Education [‘Bundeszentrale für gesundheitliche Aufklärung, BZgA’] and offers reactive telephone counselling (calls initiated by the smoker) with a maximum of five proactive follow-up calls (calls initiated by the counsellor). Trained specialists advise smokers seeking support in smoking cessation, former smokers experiencing a relapse crisis, and information seekers who intend to quit. In 2021, more than 33,000 German smokers contacted the national Smokers Quitline. In a previous evaluation, it was found that smokers who received proactive counselling (several counselling sessions) from the national German Smokers Quitline had significantly higher abstinence rates three months after the intervention than smokers who received reactive counselling (one-time counselling) (22.3% vs. 11.1%) [19]. In this study, participants were not randomly assigned to one of the two study conditions.

As the impact of the national German Smokers Quitline could be increased by optimizing the offered intervention, the overall goal of the current study is to conduct a two-arm randomized controlled trial to evaluate the effectiveness of the national German Smokers Quitline. To accomplish this, abstinence rates will be compared among smokers, who will receive proactive telephone counselling and smokers who will receive a self-help brochure. Based on previous research [15], we expect higher smoking cessation rates among participants in the telephone counselling condition compared to the control condition (primary outcome). In addition, we hypothesize that telephone counselling will increase quit attempts, the occurrence of 24-hour abstinence, the motivation to quit, the implementation of smoking restrictions at home, and reduce daily cigarette consumption and nicotine dependence levels among non-abstainers three and twelve months after start of the intervention (secondary outcomes).

## Methods

### Study design

The present evaluation is designed as a parallel-group, superiority, two-arm randomized controlled trial with 1:1 allocation ratio. The evaluation comprises three assessments within a period of approximately one year. Data collection will take place at baseline, three months (post assessment) and twelve months (follow-up assessment) after baseline assessment. The study design and participant flow are outlined in the Consolidated Standards for Reporting Trials (CONSORT) diagram (Fig. 1). After giving informed consent and completion of the baseline survey, participants will be randomly assigned to the intervention or control group. In the intervention group, participants will receive telephone counselling from counsellors of the national German Smokers Quitline, while in the control group they will be provided with a self-help brochure to support smoking cessation. Self-help materials were chosen as treatment in the control condition, as participants may have a benefit compared to receiving no intervention [20]. Moreover, it is considered unethical to recruit participants for a smoking cessation treatment when subsequently not offering an intervention. Providing an alternative intervention for the control group may also help achieve comparable response rates. To allow correction for any overreporting of abstinence, abstinence will be biochemically verified for a random sample of study participants who report abstinence at 12-month follow-up.

**Fig. 1 Fig1:**
[figure not shown]
Consolidated Standards for Reporting Trials (CONSORT) diagram: study design and participant flow

### Sample size calculation

To calculate the required sample size, a power analysis was carried out using the software G*Power [21]. Based on previous studies examining the effects of telephone smoking counselling and the use of self-help materials on seven-day-point-prevalence abstinence rates [15], a small effect size was expected. Assuming a significance level of 5% and statistical power of 0.8, the estimated required sample is *N* = 700 participants (350 participants per study condition). The calculated sample size was corrected by a 30% dropout rate [7], resulting in a total sample size of *N* = 910 enrolled participants.

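### The stated 80% power does not hold at 12 months for the long-term effect the protocol reports from the review it cites for sizing (7% to 10%): power there is about 30% with 350 per arm and 37% with 455

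*Protocol article*

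**What the plan says.** Under Sample size calculation, the protocol article refers to earlier studies of telephone counselling and self-help materials, citing the systematic review (reference 15). It continues: "a small effect size was expected. Assuming a significance level of 5% and statistical power of 0.8", which leads to N = 700, or 350 per arm. A 30% dropout correction brings enrolment to 910, or 455 per arm. The planning effect is given no number, no pair of rates and no metric, and the test is not said to be one- or two-sided.

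The Background reports the same review. Quitline callers who received proactive counselling were 1.38 times as likely to become abstinent as minimal-intervention controls; put as rates, they "increased their chances of long-term cessation (at least 6 months after start of the intervention) from 7 to 10" per cent. The last paragraph of the Background rests the primary hypothesis on this review too.

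The Primary outcomes section lists seven-day point prevalence abstinence at 3 and at 12 months and prolonged abstinence over 12 months. Under Statistical analyses, participants of unknown smoking status count as smokers, so nearly all 455 per arm enter the intention-to-treat comparison. Effect sizes and confidence intervals are to be reported.

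**The concern.** The same review supports the expected effect and, through it, the claim of 80% power. The effect the article reports from it is three percentage points on a 7% base. That is a small absolute difference for 350 per arm, and the two statements do not fit together for long-term abstinence.

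The 12-month result is at stake. The Discussion presents 12-month abstinence as the assessment closest to lifelong abstinence and links wider promotion of the quitline to its being found effective. If the true benefit is the size reported from the review, a non-significant 12-month result is more likely than not, while a reader of the sample size paragraph would credit that result with 80% power.

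**Working it through.** **The plan's own figures.** N = 700 cannot be recomputed, because the effect behind it has no stated value. The later step follows as 700 × 1.30 = 910, or 455 per arm.

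**Inputs.** Control 7% and counselling 10% (Background); 5% significance and power 0.8 (Sample size calculation); 1:1 allocation (Study design); n = 350 or 455 per arm. Sidedness is not stated, so both are shown.

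**Formula** (two proportions, pooled variance under the null):

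power = Φ[(Δ − z·SE0) / SE1], with SE0 = √(2·p̄(1 − p̄)/n) and SE1 = √((p1(1 − p1) + p2(1 − p2))/n).

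Here Δ = 0.03 and p̄ = 0.085. Then 2·p̄(1 − p̄) = 0.15555, and p1(1 − p1) + p2(1 − p2) = 0.0651 + 0.0900 = 0.1551.

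*350 per arm:* SE0 = 0.02108, SE1 = 0.02105.
- Two-sided: (0.03 − 1.96 × 0.02108)/0.02105 = −0.538, power 29.5%.
- One-sided (z = 1.645): −0.222, power 41.2%.

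*455 per arm:* SE0 = 0.01849, SE1 = 0.01846.
- Two-sided: (0.03 − 1.96 × 0.01849)/0.01846 = −0.338, power 36.8%.
- One-sided: −0.023, power 49.1%.

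Exact binomial enumeration of the uncorrected chi-square test gives the same two-sided figures, 29.5% and 36.8%. With 7% × 1.38 = 9.66% in place of the rounded 10%, two-sided power is 24.6% and 30.5%.

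**Size needed for 7% versus 10%.** n = (1.96·√0.15555 + 0.842·√0.1551)² / 0.03² = 1,356 per arm two-sided; 1,068 one-sided. These show scale only; no increase is proposed.

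**What the planned size detects with 80% two-sided power** (same formula solved for p2):

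| Control rate | 350 per arm | 455 per arm |
|---|---|---|
| 7% | 13.4% (ratio 1.91) | 12.5% |
| 10% | 17.3% (ratio 1.73) | 16.3% |

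On the arcsine scale, 7% versus 10% is h = 2·asin√0.10 − 2·asin√0.07 = 0.108. The effect that 350 per arm detects with 80% power is (1.96 + 0.842)·√(2/350) = 0.212, about twice as large.

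**Would a higher control rate rescue it?** Keeping the ratio at 1.38, two-sided:

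| Control rate | Power, 350 per arm | Power, 455 per arm |
|---|---|---|
| 10% | 34% | 42% |
| 15% | 50% | 61% |
| 20% | 66% | 77% |
| 25% | 79% | 88% |

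Power reaches 80% at a control rate of about 25.6% with 350 per arm, or 21.2% with 455: three or more times the 7% reported.

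**The case against.** The strongest objection is that the planning effect is inferred. The sample size paragraph speaks of seven-day point prevalence in earlier studies. The 7% to 10% is a summary of cessation at six months or later, among smokers who had called a quitline, against self-help or a single brief call. This trial recruits from an online panel and compares with a brochure only. The review may hold estimates closer to this setting, and that cannot be checked here. This limits the point: it shows that the stated power fails for the one effect the article reports from its sizing source, and cannot show which effect was used. A condensed article may also leave a numerical input to the full protocol, so the missing number alone would not be a finding.

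Four stronger readings are tempting, and the documents do not support them.

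- **That the shortfall covers all primary outcomes.** The reported rates are long-term and say nothing about the control rate at 3 months. The Background also cites 22.3% versus 11.1% at three months, for which 350 per arm would have 98% power. That evaluation was not randomised, had one-time counselling as comparator and is not cited for sizing, so it does not restore the 80% claim either; a ratio of 1.38 on 11.1% gives 38% to 47%.
- **That N = 700 is a miscalculation because a conventional small effect gives another number.** The article says only that "a small effect size was expected" and names neither a metric nor a value, so there is nothing to fail to reproduce.
- **That counting missing participants as smokers lowers power further.** This would require the review's rates to exclude missing participants, which the article does not say.
- **That the plan would present a null result as showing the quitline ineffective.** No passage says so, and confidence intervals are already planned.

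**Conclusion.** The concern holds for the 12-month primary abstinence outcomes. For 7% versus 10%, two-sided power is about 30% with 350 per arm and 37% with all 455 analysed; one-sided, 41% and 49%. Neither the unstated sidedness nor the full intention-to-treat number brings it near 80%. A true benefit of that size would therefore give a non-significant two-sided result about 63% to 70% of the time (1 − 0.368 and 1 − 0.295).

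This rests on two assumptions: that the Background's account of the review is the relevant long-term effect, and that its rates apply to both 12-month outcomes, since the article does not say which definition of abstinence underlies them. What is established is a mismatch between the stated power and the cited source as this article reports it. Misuse of the power software is not shown.

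**What to change.** Restate the Sample size calculation paragraph so that it:

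1. gives the two abstinence rates assumed, the time point they refer to, and whether the test is one- or two-sided;
2. says that 350 per arm has 80% two-sided power for about 7% versus 13.4%, or 10% versus 17.3%;
3. says that power for the 7% versus 10% reported from the review is about 30% to 37% at 12 months (two-sided), so that a non-significant 12-month result is to be read from the planned confidence interval and not as a null result with 80% power.

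If the planning rates came from another estimate, naming it under item 1 would explain N = 700; items 2 and 3 would still be needed. The cost is a few sentences and a less favourable power statement. Enrolment, outcomes and analyses stay as they are.

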### Data collection and management

Participants will be recruited consecutively between October 2021 and June 2022. Therefore, data collection will take place at different time points (at baseline, three months and twelve months after baseline assessment) over a period of approximately two years. Data will be collected via online questionnaires using the software SoSci Survey [46]. It is expected that the majority of questionnaires will be administered digitally (compared to phone interviews). In order to biochemically verify abstinence, 20% of study participants who will report abstinence at 12-month follow-up and who consented to participate will be randomly selected. Research staff will meet participants at their preferred location and will collect breath carbon monoxide (CO) using a portable CO monitor.

Once a participant is enrolled, the study site will make every reasonable effort to follow the participant for the entire study period. Various procedures will be used to reduce attrition, including reminder emails and calls, flexible scheduling of the counselling sessions, and incentives for completing the questionnaires. It is expected that the rate of loss-to-follow-up will not exceed the calculated 30%. To enhance validity of data, multiple methods will be used to assess intervention adherence including the phone call prior to enrolment in order to answer possible questions and questionnaire items on the use and acceptability of the received intervention at 3-month post assessment.

All participant data is handled in accordance with the General Data Protection Regulation (GDPR). All data will be maintained confidentially before, during, and after the trial and is stored securely at the study site with access only by dedicated study team members. All substantial procedures are described in the application for the Ethics Committee and can be provided on request. The final data set will be stored for 10 years after completion of the study. A data monitoring committee is not considered necessary as participants are not blinded to the study conditions and as this is a short-term, non-invasive intervention with the opportunity to quit at any time without any negative consequences or side-effects.

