### Statistical analyses

Descriptive analyses will be conducted to examine whether randomization has resulted in an equal baseline distribution of participants regarding relevant characteristics across the two conditions using *χ*^2^-tests and *t*-tests. To account for any possible group differences at baseline, confounding variables will be included in subsequent analyses. We will use logistic regression models and analyses of variance to evaluate the effectiveness of the intervention by comparing smoking cessation rates across groups. Effect sizes, as well as confidence intervals, will be reported. To analyze abstinence rates, the intention-to-treat (ITT) approach will be used. This means that data of all randomized participants will be included in the analyses unless they are deceased or have moved to an untraceable address, as recommended by the Russell Standard criteria (RS) [28]. Participants with undetermined smoking status at follow-up will be counted as smokers. In addition to the ITT principles, a complete-case analysis will be performed, in which only participants with outcome data on all assessments will be included. As all assessments use a forced entry format, no imputation for missing values will be needed. All analysis will be conducted using the statistical program R and R Studio [47, 48].

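### The 30% dropout allowance is multiplied on (700 × 1.3 = 910) rather than divided out (700/0.7 = 1000), so 910 enrolled covers only 23% loss and the complete-case analysis has about 76% power at 30% loss

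*Protocol article*

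**What the plan says.** Under Sample size calculation, the protocol says that "a small effect size was expected" and gives no abstinence rates for the calculation. It continues: "Assuming a significance level of 5% and statistical power of 0.8", the requirement is "700 participants (350 participants per study condition"). The dropout step follows: "The calculated sample size was corrected by a 30% dropout rate [7], resulting in a total sample size of" 910, described as "910 enrolled participants".

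Under Data collection and management, the 30% is explained: "It is expected that the rate of loss-to-follow-up will not exceed the calculated 30" per cent. It is thus a rate of loss among enrolled participants, used as a ceiling.

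Under Statistical analyses, abstinence is analysed by ITT. Everyone randomized is kept apart from those who have died or cannot be traced, and "Participants with undetermined smoking status at follow-up will be counted as smokers". A complete-case analysis, limited to participants with outcome data at every assessment, is added to this.

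Under Study design, the trial is a "two-arm randomized controlled trial with 1:1 allocation ratio", so 910 means 455 per arm.

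**The concern.** The purpose of a dropout correction is to have the required number left after the expected loss. Adding 30% to 700 does not do this, because the 30% is then lost from the larger number. A reader of the protocol is told that 910 protects 80% power against 30% loss. On the protocol's own figures it does not.

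There is also a mismatch with the analysis. A headcount correction suits an analysis restricted to people with outcome data. The ITT analysis of abstinence is not of that kind: non-responders stay in the denominator as smokers. Loss then acts by lowering the observed abstinence rates, not by reducing the number analysed. The sample size section does not say which basis its effect size has, so the power of the ITT analysis cannot be read from it.

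**Working it through.** **Inputs from the protocol.** Required number 700 (350 per arm), power 0.8, significance level 5%, loss 30%, enrolled 910, allocation 1:1.

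**Assumptions made here.** Two-sided test (the protocol does not state sidedness), equal loss in both arms, and control abstinence rates of 5–30%, because none are given for the calculation.

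**1. The plan's figure.** 700 × (1 + 0.30) = 910. This reproduces the stated number exactly.

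**2. The number needed.** 700 / (1 − 0.30) = 1000, or 500 per arm. That is 90 more than 910.

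**3. What 910 delivers.**
- At 30% loss: 910 × 0.70 = 637 with data (318.5 per arm), and 700 − 637 = 63 short.
- Loss that still leaves 700: 1 − 700/910 = 23.1%.

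**4. Complete-case power at 30% loss.** The effect is not stated, so take whatever effect gives 80% at 350 per arm. With n per arm, power = Φ[(1.960 + 0.842) × √(n/350) − 1.960].
- n = 350: Φ(0.842) = 80%.
- n = 318.5: 2.802 × √0.91 − 1.960 = 0.713, and Φ(0.713) = 76.2%.

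A one-sided test gives 76.6%. The complete-case set requires data at all assessments, so its loss is at least as large as the loss at any single one.

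**5. ITT power, if the assumed effect already counts missing as smokers.** The number analysed is then about 455 per arm and the effect is unchanged: 2.802 × √(455/350) − 1.960 = 1.234, and Φ(1.234) = 89%. One-sided: 88%.

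**6. ITT power, if the assumed effect refers to responders.** For each assumed control rate, find the counselling rate that gives 80% at 350 per arm, multiply both rates by 0.7, and compute power at 455 per arm. The formula is Φ[(d − 1.960 × SE₀)/SE₁], where d is the difference in rates, SE₀ uses the pooled rate and SE₁ the separate rates.

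Example with a control rate of 7%: the counselling rate that gives 80% is 13.4%. Diluted, these become 4.9% and 9.4%, with d = 0.0448, SE₀ = 0.0171 and SE₁ = 0.0170. Power is Φ(0.67) = 75%.

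| Assumed control rate among responders | Counselling rate giving 80% at 350 per arm | ITT power, 910 enrolled | ITT power, 1000 enrolled |
|---|---|---|---|
| 5% | 10.7% | 75% | 79% |
| 7% | 13.4% | 75% | 79% |
| 10% | 17.3% | 74% | 78% |
| 15% | 23.3% | 73% | 77% |
| 20% | 29.1% | 72% | 76% |
| 30% | 40.1% | 70% | 74% |

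The range is 70–75% at 910 (71–76% one-sided) and 74–79% at 1000. The counselling rates are solved for, not taken from the protocol.

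**7. Can the basis of the effect be recovered from 700?** No. The conventional small effect, h = 0.2, gives 786 in total two-sided and 620 one-sided. A total of 700 corresponds to h of about 0.212 two-sided or 0.188 one-sided, and many pairs of rates fit either value.

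**The case against.** The strongest reply is that the main analysis of abstinence does not lose the missing participants. About 910 are analysed, which is above 700, and the fall to 637 concerns only an additional analysis. This stands. A reader might infer from the arithmetic that the trial misses its 80% power in the ITT analysis as well. The documents do not support that, because the sample size section does not say whether its small effect already treats missing participants as smokers. If it does, ITT power is about 89%.

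The counter-argument is that a dropout correction makes sense only if 700 means people with outcome data, which points to the responder basis. That is a reasonable inference about intent, but the text does not establish it. The ITT figure has to stay conditional.

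It can also be said that 30% is a ceiling, that reminders, flexible scheduling and incentives are planned against attrition, and that at 23% loss or less the 700 are retained. This is true and limits the size of the problem. It does not make 910 the right figure for the 30% that the protocol names.

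A reading of the 30% as a plain recruitment margin fails, because the data collection section describes it as loss to follow-up.

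**Conclusion.** The sample size statement is wrong as written, and the severity is moderate. The part that needs no assumption about the effect size is the headcount: 910 with 30% loss leaves 637, 63 below the stated requirement, and 910 covers 23.1% loss. For complete cases this costs about 4 percentage points of power (80% to 76%), and only if loss reaches the full 30%.

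For ITT, the power is either about 89% or about 70–75%, depending on an unstated basis and on the assumptions listed above. Neither value can be asserted from the protocol. Nor should 1000 be taken as a full remedy: it gives 700 evaluable participants at 30% loss, but only 74–79% power if the rates are diluted under ITT. No analysis set, test or estimate is affected.

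**What to change.** In the sample size section:

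1. Replace the dropout sentence by one of two correct statements: that 910 enrolled retains 700 if loss is at most 23%; or that 30% loss leaves 637 evaluable, with about 76% power for the complete-case analysis.
2. Compute the ITT power on all 910 with abstinence rates that count missing participants as smokers. Report it together with those rates, the sidedness of the test and the loss assumed in each arm.
3. If enrolment can still be changed, the number that keeps 700 evaluable at 30% loss is 1000. It should be presented as that and not as a guarantee of 80% power under ITT.

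The sentence on expected loss in the data collection section should be made consistent with whichever statement is chosen. The restatement costs two or three sentences and one short calculation, with no effect on conduct. Only the optional move to 1000 costs recruitment, at 90 further participants.

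### The 30% dropout correction multiplies 700 by 1.3 instead of dividing by 0.7, so 910 enrolled leaves 637 observed at 30% loss, not 700

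*Protocol article*

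**What the plan says.** All places are in the protocol article.

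- **Sample size calculation.** The inputs are given as "Assuming a significance level of 5% and statistical power of 0.8", with the effect described only by the words "a small effect size was expected". The result is that "the estimated required sample is *N* = 700 participants (350 participants per study condition"). The next sentence says "The calculated sample size was corrected by a 30% dropout rate", for which it cites a source, "resulting in a total sample size of *N* = 910 enrolled participants".
- **Abstract, Methods.** The enrolment figure is repeated: "A total sample of 910 daily smokers".
- **Study design.** The trial is a "two-arm randomized controlled trial with 1:1 allocation ratio".
- **Data collection and management.** The 30% is tied to follow-up of enrolled participants: "It is expected that the rate of loss-to-follow-up will not exceed the calculated 30" per cent.
- **Statistical analyses.** Abstinence is analysed by intention to treat. All randomised participants are kept unless deceased or untraceable, and undetermined smoking status counts as smoking. A complete-case analysis, limited to participants with data at every assessment, is added.

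**The concern.** A dropout allowance should leave the required number with data after the expected share of enrolled participants has been lost. The protocol adds 30% of the required number instead. The two operations differ noticeably at a rate this high: adding 30% protects against a loss of about 23%, not 30%.

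Two things follow. The article presents 910 as covering 30% loss, and for observed participants it does not. A team using the Data collection section as its guide would also regard a loss of, say, 28% as within plan, although 910 × 0.72 = 655 is already below 700.

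**Working it through.** **Inputs.** Required N is 700 (350 per arm), power 0.80, significance level 5%, dropout 30% and enrolled N 910, all from the Sample size calculation section. Allocation is 1:1, from Study design. The section gives neither a numerical effect nor the sidedness of the test. I therefore take 700 as given, work with whatever effect yields 80% power there, and assume a two-sided test unless stated.

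**1. Reproducing the plan's figure.** 700 × (1 + 0.30) = 910, an exact match.

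**2. Number needed to keep 700 at 30% loss.** 700 / (1 − 0.30) = 1,000, which is 90 more than 910.

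**3. What 910 leaves.** 910 × (1 − 0.30) = 637, or 318.5 per arm. The shortfall is 700 − 637 = 63, and 63 / 700 = 9%.

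**4. Loss that 910 can absorb.** 1 − 700 / 910 = 23.1%.

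**5. Power in an analysis of observed participants.** For a fixed effect, the standardised difference scales with the square root of N. At 700 it equals 1.960 + 0.842 = 2.802. At 637:

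Φ(2.802 × √(637/700) − 1.960) = Φ(2.673 − 1.960) = Φ(0.713) = 0.762.

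A one-sided 5% test gives 0.766. The near-constancy of this figure across control rates follows from fixing 80% at 700, so it is not independent evidence about the effect.

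**6. Power of the intention-to-treat abstinence analysis at 910, missing counted as smokers.** This takes all 910 as analysed and depends on what the planning effect refers to.

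*(a) The effect already counts missing as smokers.* All 910 contribute at the planned effect:

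Φ(2.802 × √(910/700) − 1.960) = Φ(3.195 − 1.960) = Φ(1.235) = 0.89.

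*(b) The effect refers to observed outcomes, and 30% are lost in each arm.* Both quit rates are multiplied by 0.7. For each assumed control rate p1, I found the p2 that gives 80% power at 350 per arm. I then computed power at 455 per arm with 0.7·p1 and 0.7·p2 (normal approximation, pooled variance under the null):

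| Assumed control rate | Rate giving 80% at 350 per arm | Power at 910, missing = smoker |
|---|---|---|
| 5% | 10.7% | 75.1% |
| 7% | 13.4% | 74.7% |
| 10% | 17.3% | 74.2% |
| 15% | 23.3% | 73.2% |
| 20% | 29.1% | 72.2% |
| 25% | 34.7% | 71.0% |
| 30% | 40.1% | 69.7% |

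Under (b), enrolling 1,000 would give 79.0% down to 73.8% over the same range. Dividing by 0.7 would restore 700 observed participants but would not quite restore 80% for this analysis.

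**The case against.** The strongest objection is that the trial is powered on abstinence, and abstinence is analysed in all randomised participants with missing status counted as smoking. Up to 910 people enter that analysis, not 637. If the planning effect came from studies that also counted missing as smokers, no inflation was needed and 910 is generous.

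This stands as a limit on the consequence. A reader might infer from the arithmetic that the primary analysis has 637 participants and 76% power, or that 80% power and 30% loss cannot both hold in any analysis. The documents do not support either inference: 637 and 76% describe an analysis of observed participants only, and under reading 6(a) the primary analysis exceeds 80%.

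The objection does not rescue the calculation as written. Correcting 700 for dropout makes sense only if 700 means participants with data, and on that premise the wrong operation was used. Under reading 6(b) the intention-to-treat analysis also falls below 80%.

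A second inference to resist is that every analysis of observed data is smaller than planned. The protocol states no size or power for the complete-case, cognition or coping analyses. Cognitions and coping are scheduled in Table 1 at baseline and three months only, so twelve-month loss need not apply to them. The complete-case set needs data at every assessment and could fall below 637.

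Finally, 30% is presented as an expected ceiling with a cited source. It is not described as a monitored target, and the realised loss may be lower.

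**Conclusion.** The inflation is wrong as written. At 30% loss, 910 enrolled gives 637 observed, 63 (9%) fewer than the plan's own requirement, and 700 observed are kept only up to 23.1% loss. These figures rest on the protocol's numbers alone, with loss to follow-up read as a share of those enrolled. That is the natural meaning in a paragraph about following participants once enrolled.

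The cost in an analysis of observed participants is about 4 percentage points of power, taking 700 as correct for the unstated effect. The size and direction for the intention-to-treat analysis cannot be settled from the article, because it does not say how the planning effect treats missing status. Equal loss in both arms is also an assumption there.

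This is a modest error that should be corrected. It does not show that the trial is unsound or that 1,000 must be enrolled.

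**What to change.** Keep 910 and restate the Sample size calculation, for example:

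> With 910 enrolled and 30% loss, 637 participants have observed outcomes, giving about 76% power for the assumed effect in an analysis of observed participants. The 700 observed, and 80% power, are kept only if loss does not exceed about 23%.

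Beside it, state whether the planning effect already counts missing participants as smokers, and give the matching power of the intention-to-treat analysis at 910. Step 6 gives the figure for each reading; present it as resting on that assumption.

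In Data collection and management, leave the 30% expectation as it is. It is the sourced assumption, whereas 23% is only solved back from 910 and nothing shows that it is achievable. Add that power in observed data falls below 80% once loss exceeds about 23%.

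The cost is a few sentences and a less favourable power statement for observed data. No extra participants and no change to the design or analysis are needed.
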